### Questionnaires/Instruments

#### MoCA Self-Reported Questionnaire

The MoCA self-reported questionnaire is the main method used for assessing cognitive function. To objectively measure the cognitive impairment patterns of the participants, MoCA, a sensitive, time-sparing tool with high diagnostic validity, will be used to measure the degree of chemobrain. We evaluate the utility of MoCA as a chemobrain screening test for older patients with cancer who are undergoing or about to receive chemotherapy. Participants will be instructed to self-report their cognitive functions through MoCA for 5 consecutive timepoints from baseline to the end of the 8-week treatment. Statistical software will be used to analyze participants’ cognitive function information recorded in case report forms.

#### FACT-Cog Questionnaire

FACT-Cog is a subjective measure of chemobrain. The FACT-Cog is a 37-item member of the FACIT suite of questionnaires, which is made up of 4 subscales: perceived cognitive impairments (18 items), perceived cognitive abilities (7 items), impact of perceived cognitive impairment on QoL (4 items), and comments from others on cognitive function (4 items) [24]. FACT-Cog is considered a reliable and valid patient report of chemotherapy-induced cognitive symptoms. Participants are required to report their responses in FACT-Cog just the same as MoCA.

#### FACT Instrument

FACT is a 37-item self-reported instrument devised to assess the multidimensional health-related QoL in patients with cancer. It consists of 5 subscales, namely, physical, social/family, emotional, functional well-being, and additional concerns for cancer. Each item is scored on a 0 to 4 scale, and the sum of all 5 subscales ranges from 0 to 144. A higher score indicates a better QoL [12].

#### FACIT-Fatigue Self-Report Questionnaire

The FACIT-Fatigue is a valid self-reported questionnaire for assessing anemia-related fatigue in patients with cancer. This 13-item questionnaire comprises concepts related to the severity and impact of fatigue over the last 7 days, including varied fatigue-related concepts across its 13 items, allowing for a nuanced assessment.

#### EORTC QLQ-C30 Questionnaire

The EORTC QLQ-C30 will be used as a self-reported questionnaire for interpreting group-level results in older patients with cancer. The current estimates can be used to better interpret the results of clinical trials in older patients with cancer using the EORTC QLQ-C30 questionnaire.

#### FAACT Self-Administered Questionnaire

The FAACT is a self-administered questionnaire developed to assess symptoms in patients with cancer with limited food intake and decreased QoL. For FAACT, a cutoff value of ≤24 has been advised to assess anorexia based on the fact that it is the half of the maximum score than can be obtained [31].

#### FACT-BRM Screening Tool

The FACT-BRM is a brief screening tool designed to assess the QoL in patients treated with BRMs. The FACT-BRM scale will be useful for measuring QoL in older patients with cancer who are receiving treatment with BRMs.

#### Safety Assessment

Except for the sensation of soreness, numbness, swelling, and heaviness, the EA intervention will not usually cause significant discomfort or serious adverse effects, but some participants may experience pain or subcutaneous ecchymosis. Patients who have acupuncture on an empty stomach are more likely to experience dizziness. Subcutaneous ecchymosis will disappear spontaneously if the participant’s blood coagulation is normal. Patients will be reminded to avoid acupuncture on an empty stomach. The condition of each participant will be closely monitored, and if other symptoms or adverse effects occur, the investigator will ensure that the participant is receiving the appropriate treatment and is suitable to continue receiving EA. All participants in the clinical trial will be asked to evaluate the safety of the intervention, and any adverse events experienced during acupuncture treatment will be reported at each visit. The severity of adverse events will be assessed according to the Common Terminology Standard for Adverse Events v5.0 criteria [32], which are useful for determining the causal relationship between acupuncture and adverse reactions. Serious adverse events will be immediately reported to the project investigator and ethics committee. The investigator will also discuss the situation with the participant to plan any temporary discontinuation or withdrawal. The costs will be reimbursed by the investigator’s organization.

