**Results:**

Eligible participants will be randomized to the control group or the experimental group in 1:1 ratio. The primary outcome of this intervention will be the scores of the Montreal Cognitive Assessment. The secondary outcomes, that is, attentional function and working memory will be determined by the Digit Span Test scores. The quality of life of the patients and multiple functional assessments will also be evaluated. These outcomes will be measured at 2, 4, 6, and 8 weeks after the randomization.

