Emerging chemotherapy-induced cognitive impairments in older patients with cancer are likely to widen without proper early intervention tactics. In this protocol, we propose a 2-arm, prospective, randomized, assessor-blinded trial to examine the efficacy and safety of EA for chemobrain among older patients with cancer who are on or about to receive chemotherapy. The aim of this study directly contributes to the existing knowledge in this area, thereby establishing a basis for further research. Changes in the scores on MoCA [17] and the incidence of adverse events serve as the primary outcome. Scores on the Digit Span Test will be the secondary outcome for attentional function and working memory [18]. The QoL and multiple functional assessments will also be evaluated [19]. Outcomes include the MoCA, Digit Span Test, QoL, and multiple functional assessments at 2, 4, 6, and 8 weeks after randomization. Data from this efficacy trial will determine whether Chinese EA successfully improves the symptoms of chemobrain and whether these improvements could markedly reduce the various side effects caused by cytotoxic chemotherapy drugs. If successful, findings from this study might have beneﬁts in reducing chemotherapy-induced working memory impairment. Data from this study may be used to support an implementation and dissemination trial of Chinese EA within real-world behavioral health and social service settings.

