### Study Procedures

After screening, eligible participants will be enrolled and they will complete baseline assessments. Thereafter, participants will be randomly assigned to either an EA experimental group or a sham control group. EA or sham treatments will be given twice weekly for 8 weeks—a total of 16 sessions. Participants in both groups will receive routine chemotherapy provided by their oncologists, which will include the use of cytotoxic drugs. Participants will be assessed at the following timepoints (see Figure 2): baseline (T0), midpoint of main treatment (T1-T3) once every 2 weeks, and end of the 8-week main treatment (T4). Assessments include MoCA [24] + Functional Assessment of Cancer Therapy-Cognitive function (FACT-Cog) [25] for cognitive performance, FACT/Functional Assessment of Chronic Illness Therapy-Fatigue (FACIT-Fatigue) [26] for fatigue, European Organization for Research and Treatment of Cancer QoL Questionnaire-Core 30 (EORTC QLQ-C30) [27] for QoL, and Functional Assessment of Anorexia-Cachexia Therapy (FAACT)/FACT-Biologic Response Modifier (FACT-BRM) [28] for chemotherapy-related side effects. Assessments will be done prior to any procedures in that visit, including disease assessment and physician consultation.

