### Assessments

In this study, therapeutic efficiency will be assessed in terms of the following aspects: cognitive performance, fatigue, QoL, and chemotherapy-induced side effects. The primary outcome of this study is to verify whether EA is therapeutically useful for preventing chemobrain and alleviating the related symptoms and the safety of intervention. Cognitive performance will be assessed using MoCA + FACT-Cog. The secondary outcomes are as follows: QoL will be measured using EORTC QLQ-C30, fatigue will be assessed using the FACIT-Fatigue scale, and the manifestation of chemotherapy-induced side effects will be assessed using the Chemotherapy Symptom Rating Scale FAACT + FACT-BRM. All assessment scales will be evaluated by previously trained researchers at the following timepoints (see Figure 2): baseline (T0), midpoint of main treatment (T1-T3) once every 2 weeks, and end of the 8-week main treatment (T4) (a total of 5 timepoints). We will also keep a record of all the shedding cases. This study is a multidisciplinary clinical trial (across oncology and Chinese medicine disciplines) on the role of Chinese acupuncture as therapy for chemotherapy-induced cognitive impairment in older patients with cancer. If successful, findings from this study might have beneﬁts in reducing chemotherapy-induced working memory impairment. Data from this study may be used to support an implementation and dissemination trial of Chinese EA in real-world behavioral health and social service settings.

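### The safety text gives a severity scale the job of judging causality, so the method stated offers no valid basis for calling an event acupuncture-related

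*Protocol article*

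**What the plan says.** The Safety Assessment section of the protocol article states that "The severity of adverse events will be assessed according to the Common Terminology Standard for Adverse Events v5.0 criteria". The sentence then continues that these are criteria "which are useful for determining the causal relationship between acupuncture and adverse reactions". On collection, the same section says that "any adverse events experienced during acupuncture treatment will be reported at each visit". The article names no other basis for judging relatedness.

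The Introduction gives safety a prominent place: "Changes in the scores on MoCA [17] and the incidence of adverse events serve as the primary outcome". The Assessments section also counts safety within the primary outcome ("alleviating the related symptoms and the safety of intervention"). The abstract does not: "The primary outcome of this intervention will be the scores of the Montreal Cognitive Assessment".

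On background treatment, Study Procedures says: "Participants in both groups will receive routine chemotherapy provided by their oncologists, which will include the use of cytotoxic drugs". The Control Group section has the comparator needled and electrically stimulated as well, with one electrified pair on the head instead of six.

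**The concern.** By the article's own description the v5.0 criteria are a severity tool. A grade is assigned from how bad the event is. The same event gets the same grade whether it came from a needle or from a cytotoxic drug, so the grade cannot serve as a causality assessment.

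This matters more here than in many trials because all participants are on, or about to start, chemotherapy. The Discussion lists fatigue, nausea, vomiting and other symptoms as common in such patients, while Safety Assessment expects pain, bruising and dizziness from the needling. The abstract says the safety of the intervention will be evaluated, and the Discussion lists safety among the aims. A reader of the results will want to know which events acupuncture caused. If the trial reports events as acupuncture-related on the basis described, that label will not mean what it says.

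**Working it through.** No arithmetic in the plan bears on this point and there is no stated figure to reproduce. The check sets the sections side by side and asks what each can support.

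**1. What the severity criteria can support.** Safety Assessment applies them to severity. That yields a grade for each event, and hence counts by grade and by arm. The grade is fixed without reference to source, so it gives no rule for assigning an individual event to needling or to chemotherapy.

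**2. What the randomised comparison can support.** The Introduction's safety outcome is the incidence of adverse events, with no restriction to related events. As an approximation, let the components add:

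- c = incidence from chemotherapy, given in both arms (Study Procedures)
- n = incidence from needling that both arms share (Acupuncture Group, Control Group)
- e6 and e1 = incidence from electrical stimulation with six pairs and with one pair

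Experimental arm: c + n + e6

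Control arm: c + n + e1

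Difference: (c + n + e6) − (c + n + e1) = e6 − e1

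The chemotherapy term cancels, so the all-cause comparison is fair without any attribution. The shared needling term n cancels too, so the comparison says nothing about it. What remains is the effect of 6 − 1 = 5 additional electrified pairs.

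One qualification applies. The Acupuncture Group section describes the control points as mainly on the head and limbs, without the abdomen. The Control Group section says the procedure is the same apart from the number of electrified pairs. If the abdominal points are omitted in the control arm, their contribution also enters the difference. The two sections need to be reconciled, but neither reading recovers n.

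**3. What is left for attribution.** There is no arm without needling, so reactions common to both arms can be identified only by judging individual events. The article's only stated basis for that judgement is the severity criteria, which step 1 shows cannot supply it.

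**4. Whether another instrument fills the gap.** The Assessments section measures chemotherapy side effects with FAACT and FACT-BRM. These give scale scores for a patient at a visit. They do not say what caused a given adverse event.

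**The case against.** The strongest reply is that this is one loosely worded clause with no consequence for any planned analysis. Much of that stands.

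- A reader might infer that the safety part of the primary outcome is invalid. The documents do not support this. The Introduction defines it as the incidence of adverse events, not of acupuncture-related ones. Statistical Analyses specifies no analysis of a related subset, and an all-cause comparison between randomised arms needs no attribution.
- A reader might infer that relatedness will be read off the grade, with severe events blamed on one treatment and mild ones on the other. The text says only that the criteria are useful for the purpose. It states no such rule.
- A reader might infer that the unblinded acupuncturist will judge causality. The Blinding section has only the acupuncturist opening the envelope, and Safety Assessment gives follow-up of events to the investigator. Nothing assigns relatedness to the acupuncturist.
- A reader might treat every session as affected: 168 participants × 16 sessions = 2,688. That is the maximum exposure. It is not a count of events or of misattributions.
- Safety cannot be taken as settled within the primary outcome, because the abstract names the MoCA alone while the Introduction and Assessments include safety.

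It is also fair to say that a relatedness scale and its assessor are details an article commonly leaves to the full protocol and the case report form, so their absence is not the point here. The point that survives is narrower. The article does state a basis for causality, and the basis it states is wrong. A fuller document could contain a sound method, but the published sentence would still contradict it.

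**Conclusion.** The concern holds as a misassigned method in the Safety Assessment text. Under the method stated, no claim that an event is acupuncture-related has a valid basis. The all-cause comparison of adverse-event incidence between arms is unaffected, but it measures only the difference between two needled arms and cannot show reactions they share.

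The size is qualitative. No sample size, power calculation, test or estimate changes. What is affected is any relatedness label attached to an event, and so any safety statement that relies on such labels.

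This conclusion rests on three assumptions: that the v5.0 criteria are the severity tool the article says they are; that no separate relatedness method in a document not shown overrides the clause; and that events are collected over the whole 8-week treatment period in both arms. The collection sentence could also be read as covering only events during the sessions themselves. On that narrower reading the all-cause comparison would cover only events during the sessions.

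The point is worth correcting because the change is small and the sentence is wrong as it stands. It does not undermine the trial's main comparison.

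**What to change.** 1. In Safety Assessment, keep the v5.0 criteria for severity only and delete the causality clause.
2. Record relatedness as a separate, prespecified judgement for each event, rated against acupuncture and against chemotherapy. An existing investigator who is blinded to allocation should make it. The Blinding section already keeps everyone but the acupuncturist blinded, and because both arms are needled that investigator does not need to know the arm.
3. Make all-cause events by grade and arm the main safety comparison, and present related events as supportive.
4. While editing, align the abstract, Introduction and Assessments on whether safety is part of the primary outcome.

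The cost is a short edit to the protocol and one added field on the adverse-event form. There are no extra visits or staff, and treatment and sample size do not change. The article reports 11 of 168 participants recruited by October 21, 2023. Events already recorded would need to be rated in the same blinded way before allocation is revealed.

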#### Sample Size Estimation

A total of 168 older patients with cancer will be recruited, of which 84 will be in the experimental group (EA) and 84 will be in the control group. Sample size calculation:

n = [p1 (1 – p1) + p2 (1 – p2)]/(p1 – p2)] × Cp.power

Cp refers to the process capability index. In the 2-sided test, Cp.power = 10.5 when *P*<.05 is met. n is the number of patients to be recruited in each group, p1 and p2 represent the incidence in each group, and a mean difference with 95% level of significance (α) and 80% power (1 – β) is set. In older patients with cancer, the incidence of chemobrain after chemotherapy is 30%, and the reduction of chemobrain could be 10%-20% with acupuncture intervention. The sample size for each group is 84 participants, considering a 20% dropout. Therefore, the overall target sample size of 168 will be included.

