With advances in cancer treatment over the decades, the survival time of older patients with cancer has been gradually extended, and the accompanying symptoms of chemobrain have gradually drawn increasing attention [5]. Recent data have shown that chemobrain-related stress could persist for a long-term period after a systemic therapy, which is particularly relevant to older patients with cancer [6]. These individuals report chemobrain symptoms of anxiety and depressive disorder, and the number of older patients with cancer will increase dramatically in the coming future. Although data on cognitive impairment onset after chemotherapy are lacking for older patients with cancer in China, clinical practitioners have paid constant attention to the health of their constituents, given their propensity for worse physical and mental health outcomes related to chemotherapy [7]. Data suggest that up to two-thirds of older patients with cancer develop chemobrain during or after chemotherapy [8]. Most of these patients experience cognitive impairments for months, but 10%-20% of these individuals experience persistent chemobrain-related stress even after many years of completing chemotherapy. In recent years, the incidence rate of cancer in senile patients has been rising in China [9]. The problem of chemotherapy-induced cognitive dysfunction is becoming increasingly common, and there are growing concerns that chemobrain could become a threat. Therefore, it is crucial to explore an intervention that can effectively prevent and treat chemotherapy-induced cognitive impairment in older patients with tumors.

Pre-existing studies [10] have shown that some neuroprotective factors such as methylphenidate and modafinil are effective for treating chemotherapy-related cognitive impairment; however, most clinical trials on interventions for chemobrain report less access to control groups and less treatment engagement. Combo acupoint stimulation therapy is a new technique based on the theory of traditional Chinese medicine and modern biological principles. With the help of invasive or noninvasive interventions, different stimuli or drug intakes would be administered at acupuncture points, meridians, or related specific body surface sites [11].

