## Discussion

Patients with cancer may have concerns of psychiatric and digestive symptoms while undergoing or just after having recently undergone chemotherapy [3]. The most common clinical manifestations are fatigue, nausea, vomiting, dry mouth, anxiety, depression, and insomnia. More seriously, cognitive impairments with a range of neurocognitive symptoms occur frequently, including visual and verbal memory impairment, forgetfulness, difficulty concentrating, learning difficulties, and organizational and coordination dysfunction [3,4]. Since the 1980s, researchers have been studying chemotherapy-induced cognitive impairment and have given several definitions to this condition, such as postchemotherapy cognitive impairment and chemotherapy-induced cognitive dysfunction. Recently, this condition was termed as chemobrain [3-5].

Chemobrain is a frequent side effect experienced by an increasing number of older patients with cancer, and it has significantly impacted their QoL [4]. Chemobrain can be described as cognitive symptoms reported by patients with cancer in self-reported questionnaires or as cognitive changes evaluated by formal neuropsychological tests [5]. Older patients with cancer will experience cognitive impairment due to chemoradiotherapy, which will lead to a series of neurocognitive symptoms called chemobrain. Older populations have been disproportionately affected by chemobrain and have heightened negative mental health outcomes after cytotoxic chemical drug therapy [3,5,7].

According to available literature [3,14], more than 75% of patients with cancer experience cognitive impairment while undergoing chemotherapy or just after completing chemotherapy, with 15%-30% of these patients experiencing persistent symptoms for up to decades. The prevalence of postchemotherapy cognitive impairment is as high as 50%-75% among older cancer survivors [33]. In some circumstances, the cognitive impairment can be lifelong, affecting the patient’s mood, relationships, QoL, career, social activity, and family life. Considering the increasing incidence of cancer, chemobrain is quite complicated, increasingly important, and has far-reaching consequences. As the incidence of cancer survivors rises, the adverse effects of chemobrain will become more frequent, thus necessitating the need to effectively prevent and treat chemobrain.

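### The unsourced 30% control incidence behind the sample size conflicts with the protocol's own higher frequencies; at 50%-75%, a 20-point absolute reduction has about 64%-70% power, not 80%

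*Protocol article*

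**What the plan says.** The Sample Size Estimation section uses a two-proportion formula. Its stated control rate is "In older patients with cancer, the incidence of chemobrain after chemotherapy is 30" percent, with no citation. The effect is given as "the reduction of chemobrain could be 10%-20% with acupuncture intervention", without saying whether this means percentage points or a relative reduction. The error rates are "95% level of significance (α) and 80% power", and the target is 84 per group after allowing for 20% dropout.

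Other sections give different frequencies:

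- Introduction: "Data suggest that up to two-thirds of older patients with cancer develop chemobrain during or after chemotherapy".
- Discussion: "more than 75% of patients with cancer experience cognitive impairment while undergoing chemotherapy or just after completing chemotherapy".
- Discussion: "The prevalence of postchemotherapy cognitive impairment is as high as 50%-75% among older cancer survivors".
- Lower figures appear only for long-term persistence. The Discussion continues "with 15%-30% of these patients experiencing persistent symptoms for up to decades", and the Introduction gives 10%-20% with symptoms many years after chemotherapy.

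The Statistical Analyses section plans a Kaplan-Meier comparison of the incidence of cognitive deficits accumulated over 8 weeks. Impairment is defined there by a 1.5 SD criterion on MoCA and QLQ-C30. Patients are on chemotherapy or about to start it.

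**The concern.** In a two-proportion calculation the control rate p1 and the reduction together fix the variance term p1(1-p1) + p2(1-p2). For a fixed absolute reduction, that term is largest when the two rates lie around one half. A 30% control rate is therefore a favourable choice compared with 50%-75%. The article does not explain why 30% applies to the 8 weeks around chemotherapy, when its own figures for that period are higher and its lower figures describe persistence over years or decades.

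If the higher figures are nearer the truth, the trial has less power than stated even at its best-case effect. A non-significant result could then be read as evidence against electroacupuncture from a trial believed to have 80% power.

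**Working it through.** **Inputs (Sample Size Estimation unless noted).** Two-sided alpha 0.05 (the article's 95% level is read this way). Power 80%. p1 = 0.30. Reduction 10%-20%. 84 per arm with 20% dropout, so 84 × 0.8 = 67 evaluable. Allocation 1:1 (Randomization and Allocation Concealment). Alternative control rates of 50%, 66.7% and 75% come from the Introduction and Discussion; 60% is added as an interior point.

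**Step 1: the plan's own figure.** For 30% vs 10% the variance term is 0.21 + 0.09 = 0.300.

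- Formula as printed (difference not squared), with the stated "In the 2-sided test, Cp.power = 10.5": 0.300/0.20 × 10.5 = 15.75, about 16 per arm.
- Difference squared, 10.5: 0.300/0.04 × 10.5 = 78.75, so 79 per arm; 79/0.8 gives 99 with dropout.
- Difference squared, 7.849 (the constant for 80% power; 10.5 is that for 90%): 58.9, so 59 per arm; 59/0.8 gives 74 with dropout.

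None of these gives 84. Those are separate defects. Correcting them while keeping 30% makes 84 look comfortable, so the control rate has to be checked in its own right.

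**Step 2: power for 20 absolute points.**

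Unpooled: power = Φ(0.20/√(V/n) − 1.96), with V = p1(1−p1) + p2(1−p2). Pooled: power = Φ([0.20√n − 1.96√(2p̄(1−p̄))]/√V), with p̄ the mean of the two rates. The last column is the unpooled n per arm for 80% power before dropout, 7.849 × V/0.04.

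| p1 → p2 | V | Power, n = 67 (pooled / unpooled) | Power, n = 84 (pooled / unpooled) | n for 80% |
|---|---|---|---|---|
| 30% → 10% | 0.300 | 83.3% / 84.8% | 90.7% / 91.7% | 58.9 |
| 50% → 30% | 0.460 | 66.0% / 67.5% | 75.8% / 77.1% | 90.3 |
| 60% → 40% | 0.480 | 64.2% / 65.7% | 74.1% / 75.4% | 94.2 |
| 66.7% → 46.7% | 0.471 | 65.0% / 66.5% | 74.8% / 76.1% | 92.4 |
| 75% → 55% | 0.435 | 68.4% / 69.9% | 78.1% / 79.4% | 85.4 |

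The worst case is at 60%, where V is 0.480/0.300 = 1.6 times its value at 30%.

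**Step 3: where power recovers.** V falls again at high rates. On the two-proportion test, power is 81.3% / 82.6% at p1 = 80% with 84 per arm, and 79.9% / 81.5% at p1 = 87.5% with 67 per arm.

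**Step 4: log-rank check, because a Kaplan-Meier comparison is planned.** Hazard ratio = ln(1−p2)/ln(1−p1); events d = n(p1+p2); power = Φ(√(d/4)·|ln HR| − 1.96).

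| p1 | n = 67 | n = 84 |
|---|---|---|
| 30% | 88.4% | 94.2% |
| 50% | 68.2% | 77.7% |
| 60% | 66.7% | 76.4% |
| 66.7% | 68.2% | 77.7% |
| 75% | 73.0% | 82.2% |

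**Step 5: the relative reading.** With a 20% relative reduction and 67 per arm, power (unpooled) is 12% at p1 = 30% (30% vs 24%) and 47% at p1 = 75% (75% vs 60%). A 10% relative reduction gives less. Here power rises with the control rate.

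**Step 6: the lower end of the stated effect.** For 10 absolute points with 67 per arm, power (pooled) is 27% at p1 = 30%, and 21% and 24% at 50% and 75%. At this effect the control rate hardly matters.

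**The case against.** A reader might infer that the protocol contradicts itself on the same quantity, in the same population and period. The text does not support that. The two-thirds figure is an upper limit with no time window, and 30% is compatible with it. The figure above 75% is for patients with cancer in general, not older patients. The 50%-75% is a prevalence in survivors, also given as an upper range. None is an 8-week cumulative incidence under the 1.5 SD definition, and the Discussion itself notes that chemobrain may be self-reported or found by formal testing, so rates can vary with the definition. The controls are also needled, with one electrified pair, so general chemotherapy rates need not apply to them. The Abstract's statement that enrolled patients already have clinically confirmed chemobrain makes any incidence hard to interpret. All of this stands: the true control rate is unknown.

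A reader might also infer that 80% power fails because of the 30% figure however the effect is read. That does not hold. Under the relative reading 80% is missed at 30% too, and a higher control rate would help. If the ratio of 30% to 10% were held constant, power at 50% would be about 99%, but the article states no such effect.

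Nor does power fall short at every higher rate. It recovers at the rates in Step 3, and the log-rank approximation passes 80% at a 75% control rate if all 84 per arm are analysed. That no-dropout case is secondary, because the plan itself allows for 20% dropout.

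A condensed article may leave a citation to the full protocol. The missing source alone would not be a finding. What remains is that the published figures differ widely with no explanation, and the stated power depends on which is used.

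**Conclusion.** The point holds as an unexplained conflict in a design input, with a conditional consequence. Assuming a 20-point absolute reduction, two-sided alpha 0.05 and 67 evaluable per arm, power is about 83%-85% at a 30% control rate and about 64%-70% for 50%-75% (log-rank approximation 67%-73%). With all 84 per arm it is about 74%-79% on the two-proportion test. The number needed per arm for 80% power before dropout rises from 59 to 85-94 (unpooled). The stated 80% is therefore not secured across the protocol's own range of frequencies, even at its most favourable effect. The figures do not show what the true control rate is, and they do not attribute a shortfall under the relative reading to the 30%.

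**What to change.** Keep 168 patients. Reconcile the Introduction, Sample Size Estimation and Discussion so that the control rate used is explained against the other figures. Either cite a source showing that 30% is the 8-week incidence under the trial's own definition of impairment, or replace it. State whether the 10%-20% reduction is absolute or relative. In place of the unconditional 80%, give power over the plausible range of control rates; for a 20-point absolute reduction with 67 evaluable per arm this is about 64%-70% at 50%-75%.

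The cost is a few sentences and a less favourable stated power. No extra patients, visits or procedures are needed.
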